### Administration

The following procedures will be performed by the surgeon for administration of the intervention.

A clinical examination under anesthesia with an anal fistula probe will be conducted to rule out active infection, anal stenosis, or active proctitis and confirm the presence of a single fistula tract.The seton will be removed, the fistula tract curetted vigorously to remove granulation tissue lining the tract, and the tract will be flushed with saline.The fistula tract length and diameter and amount of the sphincter muscle involved will be assessed by the surgeon with an anal fistula probe placed from the external to the internal opening.The appropriate model collagen matrix will be used based on the length of the tract.The collagen will be saturated with the rhPDGF solution in a sterile dish for a minimum of 10 min.After the collagen is fully saturated with rhPDGF, it will be pulled through the fistula tract carefully from the internal opening to the external opening.The collagen will be sutured to the rectal mucosa at the internal opening and any portion beyond the skin level will be trimmed to sit flush with the external opening.

### Outcomes

#### Primary outcome

The primary outcome of this study will be to evaluate the technical performance of rhPDGF-enhanced collagen implantation for treatment of complex perianal fistulas. This will be measured by the proportion of participants with procedural success as defined by implantation of the intervention without any intervention-related serious adverse events (SAEs) within 3 months of the procedure. The 3-month endpoint is the average timepoint when the surgeon makes the diagnosis that the perianal fistula has completely healed or failed to heal.

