### Intervention

rhPDGF is highly purified, aseptically processed, and sterile filled into transparent glass syringes. One syringe contains a 0.5 mL solution of 0.3 mg/mL rhPDGF in 20 mM sodium acetate buffer pH6+/−0.5. rhPDGF is stored at 2°C to 8°C and then allowed to reach room temperature prior to administration to the patient. Up to 4 mL of the rhPDGF (0.15–1.2 mg) solution will be used to rehydrate a collagen matrix manufactured from porcine collagen sourced from veterinary pigs. The native collagen molecules and fiber structures are maintained, and no additional materials are added. Antigens, lipids, and non-collagenous proteins are removed through extraction and purification steps rendering the material acellular and reducing the likelihood of acute and chronic biological reactions. The collagen membranes are available in three different sizes: 20×30 mm (model 500662), 30×40 mm (model 500663), and 40×50 mm (model 500664) and can be trimmed as needed. All components of the intervention are biocompatible and absorbable and will only be implanted once.

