#### Secondary outcomes

The secondary outcomes of this study will be used to assess the preliminary safety and efficacy of rhPDGF-enhanced collagen for treatment of complex perianal fistulas. A quantitative and descriptive summary of all intervention-related adverse events (AEs) within 3 months of the procedure will be used to assess preliminary safety. Clinical evaluation of fistula healing assessed as healed/not healed by no drainage/drainage from the external opening at the Month 3 follow-up visit will determine the proportion of fistulas healed. Rate of recurrence is assessed by the number of participants with clinically diagnosed healed fistulas (no drainage/no leakage) that are later diagnosed with recurrence at the final, Month 6 study visit. The Month 6 endpoint was chosen because successful treatment of complex perianal fistulas is based not only on a diagnosis of being completely healed by clinical exam but also on clinical remission without recurrence, and the majority of recurrences occur within 6 months of the treatment. Safety and efficacy will also be assessed by the change in patient-reported pain, incontinence, and other perianal fistula-related symptoms in the baseline and weekly follow-up participant surveys.

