### Study Assessments and Procedures

#### Safety Assessments

Clinical examination
At screening, during the procedure, and at all follow-up visits, clinical examination of the perianal fistula will visually assess for infection, excess drainage, chronic inflammation, abnormal bleeding, or fibrosis at the external opening. Photographs of the external openings will be taken at screening and all follow-up visits to document healing progress.Patient medical history
At screening, patients meeting inclusion criteria will be screened for exclusion criteria through their medical history. The etiology of the perianal fistula will also be discussed and documented. Participants will review any known allergies, previous surgical procedures, previous complications, and frequency of fistula occurrence or recurrence.Pregnancy test
At screening, women of childbearing potential will be required to take a pregnancy test and must agree to use two reliable contraceptive methods for the duration of their participation in the study, one of which must be a barrier method; the contraceptive methods will be documented in the screening eCRFs.Crohn’s Concomitant Medications
At screening and all follow-up visits, Crohn’s medications will be documented for patients with CD-related perianal fistulas, including medication name, single dose amount, route, frequency, start date, and end date.Participant survey
At screening, baseline, and weekly following the procedure till Month 3, participants will complete a self-report questionnaire assessing the frequency and severity of pain, incontinence, and other perianal fistula-related symptoms. If symptoms are increasing in frequency and severity, an off-cycle clinical visit will be scheduled to address any adverse events.Assessment of adverse events
The following adverse events will be recorded in the eCRFs and followed until resolution:
Adverse events that are classified as related to study procedures (that is, potentially-, probably-, or definitely related to study procedures or of uncertain relationship to study procedures), regardless of severitySerious adverse events regardless of relatedness to study procedures.Clinical adverse events, events diagnosed as clinical conditions, with a severity grade ≥ 3, regardless of relatedness to study procedures.

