#### Sample Size

This study will aim to recruit and screen 60 eligible patients to enroll and randomize 12 participants in a 2:1 ratio. Sample size was influenced by expected confidence interval widths for the primary outcome (technical performance of the rhPDGF-BB-enhanced collagen implant for treatment of complex perianal fistulas). Assuming that all 8 participants assigned to the intervention arm will achieve successful implementation of the treatment, the lower bound of a Clopper-Pearson 95% confidence interval would be 0.63, indicating high confidence that the treatment does not have a low probability of successful implementation. Sample size was also influenced by the efficacy outcome of healing at 3 months. Based on the prior work in the literature, we assume that the routine care arm (across the expected distribution of routine care procedures) will achieve 50% healed at 3 months (2/4 healed). If 7 of the 8 intervention arm patients achieve healing, the expected lower bound of a Carlin-Louis 95% confidence interval for the differences in proportions healed would be about −0.14, indicating high confidence that the intervention does not cause substantial harm. Furthermore, if all 8 intervention arm patients achieve healing, the expected interval lower bound will be −0.01, such that there is high confidence of treatment benefit.

We assumed that study dropout before Month 3 will not occur, and that crossover into the intervention arm will not occur until after ascertainment of Month 3 outcomes. The time-to-healing will be considered for secondary analyses and likely have slightly higher power assuming that patient-reported data is accurate and high quality, as it achieves higher granularity to assess healing than the binary outcome of healing at Month 3 follow-up. Likewise, exploratory analyses including crossover patients may improve power for assessing the primary outcome. Other secondary endpoints and subgroup analyses are exploratory in nature, and we did not perform formal power analyses for these.

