#### Primary Outcomes Analysis

The primary endpoint is technical performance of the treatment. This will be reported as the proportion of participants assigned to the treatment arm with successful implementation of the treatment (without SAEs). This will be reported along with a Carlin-Louis 95% confidence interval.

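### The primary endpoint does not count removal of the implant as a failure unless it is an intervention-related SAE, although the protocol itself foresees removal for infection or abscess

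*Protocol article*

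**What the plan says.** The Primary outcome section sets out to "evaluate the technical performance of rhPDGF-enhanced collagen implantation for treatment of complex perianal fistulas" and measures this by procedural success, meaning "implantation of the intervention without any intervention-related serious adverse events (SAEs) within 3 months of the procedure". The Abstract gives the same two elements. The Primary Outcomes Analysis section restates the endpoint as the "proportion of participants assigned to the treatment arm with successful implementation of the treatment (without SAEs"), with a Carlin-Louis 95% interval. That wording drops the requirement that the SAE be related, but adds nothing about the implant afterwards. None of the three places mentions whether the implant stays in or is taken out.

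The section Participant Discontinuation/Withdrawal from the Study lists, as its own reason, an infection or abscess that makes it necessary to take the plug out and proceed to routine care. It lists unacceptable adverse events as a different reason. It does not say whether such a removal is serious, or how the participant then counts in the primary proportion.

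On precision, the Sample Size section takes 8 successes out of 8 and a Clopper-Pearson lower bound of 0.63, "indicating high confidence that the treatment does not have a low probability of successful implementation".

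Other parts of the trial pick up some of this. The Secondary outcomes section includes "A quantitative and descriptive summary of all intervention-related adverse events (AEs) within 3 months of the procedure", and healing at Month 3 is a further secondary outcome. The Safety Assessments section records "Adverse events that are classified as related to study procedures" at any severity. The Intervention section states: "All components of the intervention are biocompatible and absorbable and will only be implanted once".

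**The concern.** Once the collagen has been placed, the only way a participant can fail the primary endpoint during the 3-month window is through an SAE. The protocol anticipates a technical failure of another kind: the implant has to come out and the participant goes on to routine care. If that episode is not classed as an intervention-related SAE, the participant is reported as a success of a product that is no longer there.

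The primary proportion is the main evidence on technical performance that this pilot will pass to a larger trial. With 8 participants in the arm, one reclassification changes the message considerably. A reader who sees 8/8 with a lower bound of 0.63 could not tell from that result whether any plug had been removed. Month 3 healing does not settle it, because it does not distinguish a removed implant from one that stayed in and did not work.

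**Working it through.** **Inputs from the article.** Total of 12 participants randomized 2:1, so 8 in the intervention arm; two-sided 95% intervals; no dropout before Month 3 assumed (Statistical analysis and Sample Size sections).

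**Input not in the article.** The number k of plugs removed within 3 months without an intervention-related SAE. No rate is given, so k = 0, 1 and 2 are assumed.

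**The plan's own figure.** For x = n = 8 the Clopper-Pearson lower bound p solves p^8 = 0.025, so p = 0.025^(1/8) = 0.6306. The stated 0.63 is correct.

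**With removals scored as failures.** The lower bound p solves P(X ≥ 8 − k) = 0.025 for X binomial(8, p), which is the 2.5% quantile of Beta(8 − k, k + 1).

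- k = 1: 8p^7(1 − p) + p^8 = 0.025 gives p = 0.4735.
- k = 2: 28p^6(1 − p)^2 + 8p^7(1 − p) + p^8 = 0.025 gives p = 0.3491.

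| Removals without related SAE (assumed) | Written definition | Removal scored as failure |
|---|---|---|
| 0 | 8/8, lower bound 0.63 | 8/8 = 1.00, lower bound 0.63 |
| 1 | 8/8, lower bound 0.63 | 7/8 = 0.875, lower bound 0.47 |
| 2 | 8/8, lower bound 0.63 | 6/8 = 0.75, lower bound 0.35 |

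The middle column assumes that no related SAE occurs.

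**The interval named for the analysis.** The Primary Outcomes Analysis section specifies a Carlin-Louis interval. Taking this as an equal-tailed interval with a uniform prior (an assumption, though it reproduces the healing-difference bounds in the Sample Size section: −0.144 and −0.008 against the stated −0.14 and −0.01), the lower bounds are 0.66, 0.52 and 0.40 for 8/8, 7/8 and 6/8. The pattern is the same.

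**How likely a discrepancy is.** If each participant has probability q of a removal without a related SAE, the chance that at least one of 8 is scored a success despite it is 1 − (1 − q)^8. This is 34% at q = 5%, 57% at 10% and 83% at 20%. All three values of q are assumptions.

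**The case against.** The strongest reply is that there is no contradiction. The article names its construct, procedural success of implantation, and defines it. It attaches 0.63 only to successful implementation and nowhere claims to measure retention. That is fair as far as it goes: the figure is right for the endpoint as written. What remains is that the protocol foresees plug removal and leaves it outside an endpoint labelled technical performance that runs for 3 months.

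A reader might infer that the endpoint cannot register loss of the implant at all. The documents do not support that. Loss or removal that is, or comes with, an intervention-related SAE within 3 months is a failure. An infection that requires removal and further treatment may well be classed as serious. The article gives no SAE definition and refers to an unabridged protocol that is not shown, so the unscored case may be uncommon.

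A reader might also infer that collagen falling out is a known weakness that the endpoint hides, and that an extrusion criterion should be added. Extrusion is not mentioned anywhere in the article and has no stated rate. The matrix is absorbable, no absorption time is given, and follow-up examination is visual at the external opening. A check at Month 1 could mistake absorption for loss and so add misclassification to a primary endpoint with n = 8.

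Finally, the trial is not blind to these events. Related adverse events of any severity and Month 3 healing are secondary outcomes, and removal is a listed discontinuation reason. This lowers the stakes, but it does not make the primary proportion show a removal.

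**Conclusion.** The point holds in a limited form. As written, the primary endpoint scores a participant whose plug is removed for infection or abscess as a technical success unless the episode is an intervention-related SAE, and the plan does not say that this is intended. One such removal among 8 would move the result from 8/8 (lower bound 0.63) to 7/8 (0.47), and two would move it to 6/8 (0.35).

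These sizes rest on assumed counts and on at least some removals not being classed as related SAEs; neither can be verified from the article. The sample size calculation is not in error. The gap is in the scoring rule and can be closed with data that the protocol already has reason to collect.

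**What to change.** Before outcomes are analysed, do one of the following:

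1. State in the Primary outcome and Primary Outcomes Analysis sections that removal of the plug within 3 months, under the infection or abscess reason in the discontinuation section, is scored as not a procedural success.
2. If the registered primary endpoint is to stay unchanged, pre-specify a supportive analysis that scores such removals as failures, reported with the same interval as the primary.

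In either case, report separately the numbers with implantation completed, with the plug removed, and with an intervention-related SAE. Any early expulsion that happens to be observed can be listed descriptively. Do not add a Month 1 extrusion criterion to the primary endpoint.

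The change concerns outcome scoring only and leaves the clinical handling of infection as it is. There are two costs. The success proportion may be less favourable. The rule also needs a dated, documented amendment in a trial that began enrolling in November 2024, so option 1 may draw questions about changing a primary endpoint after randomization started. Option 2 avoids that at the price of a second reported proportion.

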#### Secondary outcomes

The secondary outcomes of this study will be used to assess the preliminary safety and efficacy of rhPDGF-enhanced collagen for treatment of complex perianal fistulas. A quantitative and descriptive summary of all intervention-related adverse events (AEs) within 3 months of the procedure will be used to assess preliminary safety. Clinical evaluation of fistula healing assessed as healed/not healed by no drainage/drainage from the external opening at the Month 3 follow-up visit will determine the proportion of fistulas healed. Rate of recurrence is assessed by the number of participants with clinically diagnosed healed fistulas (no drainage/no leakage) that are later diagnosed with recurrence at the final, Month 6 study visit. The Month 6 endpoint was chosen because successful treatment of complex perianal fistulas is based not only on a diagnosis of being completely healed by clinical exam but also on clinical remission without recurrence, and the majority of recurrences occur within 6 months of the treatment. Safety and efficacy will also be assessed by the change in patient-reported pain, incontinence, and other perianal fistula-related symptoms in the baseline and weekly follow-up participant surveys.

#### Tertiary outcomes

The tertiary outcomes of this study will assess the feasibility of studying rhPDGF-enhanced collagen for treatment of complex perianal fistulas in a larger efficacy trial. This will be determined by total number of participants recruited and eligible, number of participants randomized per month, and the proportion of participants retained at Month 3 and Month 6.

#### Crossovers

If the fistula is not healed at the Month 3 study visit and the participant is in the control arm of the study, they will reach their endpoint as a control and have the option to crossover to the investigational arm and receive the rhPDGF-enhanced collagen treatment. These participants will first have another draining seton placed in their fistula tract for approximately 4 weeks and be scheduled for implantation of the rhPDGF-enhanced collagen. This group will restart the schedule of activities at visit 2 for the procedure and return for all post-procedural study visits 3–5 at Months 1, 3, and 6. Their outcome measures will be tracked and documented, and they will complete the weekly participant surveys, but their results will not be included in the initial primary analyses of the original randomized participant data. This will be considered extended, open-label use of the investigational intervention and will not delay reporting the outcomes from the comparison of healing between the original intervention and control groups at Month 3. Their outcome measures will be analyzed and reported later.

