## METHODS

### Trial design

This study will be carried out in accordance with International Conference on Harmonisation Good Clinical Practice (ICH GCP) and the United States (US) Code of Federal Regulations (CFR) applicable to clinical studies (45 CFR Part 46, 21 CFR Part 50, 21 CFR Part 56, 21 CFR Part 312, and/or 21 CFR Part 812). This Phase II clinical trial will evaluate the performance, preliminary safety and efficacy, and feasibility of rhPDGF-enhanced collagen on healing complex perianal fistulas that are not eligible for a fistulotomy in patients 21 years of age and older. This prospective, blinded, single-site study is expected to enroll and randomize 12 participants at a 2:1 intervention versus control allocation ratio stratified by fistula etiology, idiopathic versus CD-related. The two arms will compare implantation of the rhPDGF-enhanced collagen to routine care procedures, which include COOK Biotech’s Biodesign^®^ Anal Fistula Plug implant for idiopathic fistulas or draining seton removal and natural healing for CD-related fistulas. Following the baseline procedure, patients will be evaluated at Months 1, 3, and 6 to assess healing of the external fistula opening and change in pain, incontinence, and other perianal fistula-related symptoms. Patients randomized to the control group who fail to heal at Month 3 will have the option to crossover to the intervention group and receive the rhPDGF-enhanced collagen intervention. The Standard Protocol Items: Recommendations for Interventional Trials (SPIRIT) schedule of enrollment, intervention, and assessments is included as Figure 1. A graphic study timeline of events is provided in Figure 2. The SPIRIT checklist is included in S1 Appendix. A full accounting of evaluations and unabridged protocol approved by the IRB is available in S2 Appendix (December 13, 2024; version 6.1) and important protocol modifications will be available from the corresponding author and by viewing the ClinicalTrials.gov (NCT06632418) study entry. A sample consent form is included in S3 Appendix.

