### Randomization and Blinding

Randomization will occur at the baseline visit at a ratio of 2:1 intervention versus control. Randomization will be stratified to achieve balance in treatment allocation across idiopathic and CD-related fistula types. Because the total sample size is 12, randomization will be blocked using blocks of size 3 (2:1 intervention to control) within each stratum (idiopathic versus CD-related). Based on historical clinical data we anticipate enrolling 9 Chron’s participants and 3 idiopathic participants. Blinding of the patients, surgeons other than the investigator performing the procedure, and study team members assessing outcomes to study arm allocation will be employed to reduce bias in conducting study activities and evaluations. Given that the control group will be receiving a routine care procedure, the investigator who will be performing all procedures will be unblinded to the treatment assignment for each participant. To maintain blinding while assessing outcomes, clinical exams during follow-up study visits will be performed by another surgeon not involved in the initial screening visit or the procedural encounter. In the case of a serious adverse event or medical emergency in which knowledge of the treatment is necessary for the participant’s well-being or medical care, the unblinded investigator will be alerted to ensure appropriate medical management.

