Tertiary outcomes will be reported as totals or proportions, as appropriate. Analyses of proportions retained at 3 months and 6 months will be similar to those for the primary outcome. Exploratory analyses which consider outcomes of participants who cross over into the investigational device arm will be reported separately or included in sensitivity analyses.

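### Controls-only crossover, repeat visits to the blinded examiner and fixed blocks of 3 can together make the arm of intervention block-mates deducible before their Month 3 and Month 6 exams

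*Protocol article*

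**What the plan says.** Trial design limits crossover to one arm: "Patients randomized to the control group who fail to heal at Month 3 will have the option to crossover to the intervention group". Under Crossovers, such participants "they will reach their endpoint as a control and have the option to crossover to the investigational arm", first have "another draining seton placed in their fistula tract for approximately 4 weeks", and then: "This group will restart the schedule of activities at visit 2 for the procedure and return for all post-procedural study visits 3–5". The same section says of the crossover phase: "This will be considered extended, open-label use of the investigational intervention". It also says that "their results will not be included in the initial primary analyses of the original randomized participant data". Secondary and Tertiary Outcomes Analysis adds that crossover outcomes "will be reported separately or included in sensitivity analyses".

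Randomization and Blinding protects outcome assessment by separating roles: "clinical exams during follow-up study visits will be performed by another surgeon not involved in the initial screening visit or the procedural encounter". It also fixes blocks of 3 (2:1) within each etiology stratum, expects 9 Crohn's (CD) and 3 idiopathic participants, and states that the operating investigator is unblinded. The Discussion calls the trial double-blind and aims to complete enrolment in about 15 months. Recruitment and Consent expects 1–2 participants per month.

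**The concern.** Each rule is reasonable alone; the difficulty lies in the combination. Crossover is open to controls only, so someone who returns for a second series of post-procedure visits is recognisably a former control. As written, those visits go to the blinded examiner. A block of 3 holds exactly one control, so identifying it settles the arm of the other two. Enrolment is staggered, so some of those two will still be waiting for a randomized exam.

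Month 3 healing and Month 6 recurrence both rest on a clinical judgement of the external opening. Everyone who becomes deducible in this way is on rhPDGF, so any expectation bias would act on one arm only. With 8 against 4 participants, a single call matters. In the Sample Size section, moving from 7/8 to 8/8 healed shifts the lower bound for the difference from about −0.14 to −0.01, and the article's reading changes from no substantial harm to benefit.

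**Working it through.** **The plan's own figures.** The article gives no figure for exposure of the blind. The precision figures used above for scale do reproduce. The Clopper-Pearson lower bound for 8/8 is 0.025^(1/8) = 0.631 (stated 0.63). Equal-tailed posterior intervals with uniform priors give lower bounds of −0.144 for 7/8 against 2/4 and −0.008 for 8/8 against 2/4 (stated −0.14 and −0.01).

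**Inputs from the article.** 9 CD and 3 idiopathic participants in blocks of 3 make 3 + 1 = 4 blocks, with 4 controls and 8 intervention participants. Control healing is 50%. The crossover procedure follows about 4 weeks of seton, and the first crossover exam comes a month after that. Accrual is 1–2 per month, or 12 over about 15 months.

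**Assumptions not in the article.** Every eligible control crosses over (50% uptake is shown as an alternative), arrivals are random, and the examiner knows block size, stratum and enrolment order. The moment of the reveal is not given, so three are shown.

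**Step 1: the deduction.** Before any reveal, a participant's chance of being on intervention is 2/3. Once a block-mate is known to be the control, it is 1.

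**Step 2: how many become deducible.** 4 blocks × 0.5 failure × full uptake = 2 crossovers. Each fixes 2 block-mates, so 4 of 8.

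**Step 3: whose exam is still to come.** Let d be the months by which a block-mate enrols after the control (negative if before), and let the reveal fall L months after the control's Month 3 visit. The block-mate's Month 3 exam follows the reveal if d + 3 > 3 + L, that is d > L. The Month 6 exam follows it if d + 6 > 3 + L, that is d > L − 3. L = 0 is the offer, L = 1 the crossover procedure and L = 2 the first crossover exam.

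- *L = 0, Month 3.* Only later-enrolled block-mates count: 2, 1 or 0 as the control is first, second or third, with mean 1. So 4 × 0.5 × 1 = 2.0, whatever the accrual pattern.
- *L = 0, Month 6, even spacing over 15 months.* CD spacing is 15/9 = 1.67 months, giving counts 2, 2, 1 (mean 1.67). Idiopathic spacing is 15/3 = 5 months, giving 2, 1, 0 (mean 1). So (3 × 1.67 + 1) × 0.5 = 3.0.
- *L = 2, even spacing.* Month 3: CD 1, 0, 0 (mean 0.33) and idiopathic 2, 1, 0 (mean 1), so (3 × 0.33 + 1) × 0.5 = 1.0. Month 6: only later block-mates count, so 4 × 1 × 0.5 = 2.0.

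**Step 4: random arrivals (simulation, 40,000 trials per setting).** Expected intervention exams after the reveal, at full uptake:

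| Reveal | Month 3: over 15 months / 1 per month / 2 per month | Month 6: over 15 months / 1 per month / 2 per month |
|---|---|---|
| Offer (L = 0) | 2.0 / 2.0 / 2.0 | 3.3 / 3.4 / 3.8 |
| Crossover procedure (L = 1) | 1.4 / 1.3 / 0.9 | 3.0 / 3.1 / 3.6 |
| First crossover exam (L = 2) | 1.0 / 0.9 / 0.4 | 2.6 / 2.7 / 3.1 |

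At 50% uptake every entry halves, giving ranges of 0.2–1.0 for Month 3 and 1.3–1.9 for Month 6.

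**Step 5: which Month 6 exams bear on recurrence.** Only participants healed at Month 3 can have a recurrence. At the plan's illustrative 7/8 healed, 2.6–3.8 becomes 2.6 × 0.875 = 2.3 to 3.8 × 0.875 = 3.3.

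**The case against.** Three stronger readings are tempting, and the article does not support them.

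- *The crossovers' own outcomes are unblinded.* They reach their control endpoint before the option arises, and Sample Size assumes that crossover follows ascertainment of Month 3 outcomes. Their later exams are declared open-label and kept out of the initial primary analyses. Knowing their arm by then breaks no stated blind.
- *The offer, or its absence, unblinds every unhealed participant.* It may reveal their arm, but their healing result is already recorded, they cannot contribute a recurrence, and the weekly surveys end at Month 3. None of these randomized outcomes is left to bias.
- *The examiner will know the block-mates' arm.* Nothing in the article gives the examiner the enrolment sequence. Counting blocks is also unreliable: randomization is at the baseline visit, and participants whose device cannot be implanted are classed as screen failures, so a slot may be filled by someone the follow-up examiner never meets. The arm can become deducible; it does not automatically become known.

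It is also fair to say that the article does not name one surgeon for all follow-up, and that the full protocol in its S2 Appendix may separate crossover visits. If the examiner learns of a crossover only at its first post-procedure exam, the Month 3 exposure is the lower figure, 0.4–1.0 exams.

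What remains is a conflict between stated rules rather than missing detail. The article sends crossovers back through visits 3–5, assigns follow-up exams to the blinded surgeon without exception, and publishes a block size that makes the inference exact for anyone who can place participants in blocks.

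**Conclusion.** The point holds for the intervention block-mates of a crossover, at their pending Month 3 healing and Month 6 recurrence exams. The primary endpoint, implantation without related serious adverse events, does not use the healing exam and is untouched.

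With 50% control failure, full uptake and an examiner able to reconstruct blocks, about 4 of 8 intervention participants become deducible. Under random arrivals, about 0.4–2.0 Month 3 exams and 2.6–3.8 Month 6 exams follow the reveal. Perfectly even enrolment with the latest reveal would lower the Month 6 figure to 2.0, and 50% uptake halves all of these. Recurrence is therefore more exposed than healing.

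A reader might conclude that blinded assessment is lost altogether. The figures do not show that: at least 6 of the 8 intervention Month 3 exams are expected to precede any possible deduction. They show an avoidable, one-sided exposure in two efficacy outcomes of a very small trial. It should be closed, because closing it costs little.

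**What to change.** Amend Randomization and Blinding and Crossovers to state that:

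1. the blinded examiner records and locks the Month 3 healing result before anyone checks allocation;
2. the operating investigator, who is already unblinded, checks allocation and makes the crossover offer;
3. crossover visits 3–5 are examined by that investigator or by other existing staff who assess no randomized participants;
4. crossover status and enrolment order are withheld from the blinded examiner until the last randomized Month 6 exam is recorded.

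The crossover rule itself does not change. The cost is protocol wording and a reassignment of visits among existing staff. The article describes the trial as ongoing, with data collection ending between August and December 2026, so exams still pending can be protected.

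The downside is that crossover outcomes may be rated unblinded, which the open-label label already accepts. Any sensitivity analysis that includes them should be labelled as mixing blinded and unblinded ratings. If the full protocol already contains these safeguards, one sentence in each of the two sections is enough.
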